## Abstract

(1) Background: Work stress is one of the most relevant issues in public health. It has a significant impact on health, especially the development of mental disorders, causing occupational imbalance. There is a growing interest in the development of tools with a positive effect on workers. To this end, wearable technology is becoming increasingly popular, as it measures biometric variables like heartbeat, activity, and sleep. This information may be used to assess the stress a person is suffering, which could allow the development of stress coping strategies, both at a professional and personal level. (2) Methods: This paper describes an observational, analytical, and longitudinal study which will be set at a research center in A Coruña, Spain. Various scales and questionnaires will be filled in by the participants throughout the study. For the statistical analysis, specific methods will be used to evaluate the association between numerical and categorical variables. (3) Discussion: This study will lay the foundation for a bigger, more complete study to assess occupational stress in different work environments. This will allow us to begin to understand how occupational stress influences daily life activity and occupational balance, which could directly enhance the quality of life of workers if the necessary measures are taken.

## 1. Introduction

Work is one of the most significant areas of occupation in adulthood, and has great relevance at a social and personal level throughout life [1,2]. Work and working conditions have a significant impact on health [3]. Stressful situations occur in the worker when these conditions are altered by different factors (work overload, lack of support, work schedules, or lack of family reconciliation) [4,5,6], giving rise to a specific type of stress called work stress [7,8]. Work stress is defined as “the reaction that the individual may have to work demands and pressures that do not match his knowledge and skills, and that test his ability to cope with the situation” [9].

It is estimated that work stress affects three million workers worldwide [10], and that it represents between 50–60% of the cases of absenteeism and presenteeism [11,12]. In addition, several studies have reported that the health sector suffers the most from this type of problem [13,14,15]. In line with this data, occupational stress has become one of the most relevant problems for public and occupational health [16,17,18].

Work-related stress has important repercussions at the personal and health levels, but also at the social level [19]. Several studies have reported that work-related stress is a trigger for mental disorders (specifically depression [14,20,21], sleep disorders [22,23], heart and/or respiratory diseases, and physical or cognitive fatigue [24,25]. Moreover, if work-related stress is prolonged and worsened over time, it can lead to burnout in the worker [26,27]. Burnout was defined by Maslach, Schaufeli, and Leiter as “a prolonged response to chronic emotional and interpersonal stressors at work, defined by the dimensions of exhaustion and inefficiency” [28].

In addition to the physical or psychological effects that work stress can have, it is also related to alterations in the occupational balance [29], defined as “a balance of engagement in occupation that leads to well-being. The balance may be among physical, mental, and social occupations; between chosen and obligatory occupations; between strenuous and restful occupations; or between doing and being” [30,31]. Several studies refer to the fact that workers experiencing occupational stress are not able to relativize work and everyday occupations, prioritizing paid employment and leaving aside activities related to social interactions, household management, and rest or sleep [29,32,33].

Some studies have associated alterations in occupational balance with perceived stress [17,32]. Both concepts include the demands, needs, and emotions associated with daily life activities, in order to obtain satisfaction and well-being [32]. Studies such as that by Yu Yu et al. have emphasized the analysis of perceived stress [34,35], defined as “the individual’s ability to cope with stressful situations” [36]. Its analysis can help us to understand different predictors of stress, and prevent alterations that lead to an occupational imbalance [17].

The effects derived from work stress suppose important direct and indirect consequences for public health [16,37]. They generate an expense to the system due to high demand on health services, and the necessity of treatments that must be maintained in the long term like antidepressants or anxiolytics, which have a minimum duration of several months [38,39]. In addition, there is an economic cost since factors associated with occupational stress, such as low self-esteem, dissatisfaction, and low efficiency in the labor field, affect short-term productivity [40,41]. In the long term, the consequences can be aggravated by the occurrence of workplace accidents or temporary or permanent disabilities, with these representing one of the main causes of early retirement [42,43,44].

Due to the aforementioned, various organizations associated with health and work have the objective of promoting quality of life and well-being, as well as greater productivity, in the worker [11,45]. They consider of interest the creation of strategies and technological solutions for the early detection and control of factors and effects associated with work stress, as well as balance between personal and work life and the promotion of healthy habits [13,46].

Studies related to occupational stress have focused on the measurement of various physiological parameters for the detection of stress [47]. The most common biomarkers and indicators of stress are blood pressure and heart rate, which have been measured in these studies through the use of non-intrusive sensors to determine stress levels in workers [48,49]. However, these devices are generally uncomfortable for the user to carry for a long period of time, as is the case of belt-format pulsometers or portable electrocardiogram (EGC) devices [47,50]. Thus, it is necessary to find new sensors that are comfortable for the user, while providing information of equal quality [51].

In recent years, wearable devices for continuous, real-time monitoring of different parameters have been developed [52]. The measurement of parameters such as sleep and physical activity can be used to identify behavioral patterns of people when they are exposed to stressful situations [52]. Currently, the literature on the use of wearables for the measurement of occupational stress is focused on the development of automatic systems for the accurate assessment of stress, but less on the benefits of the study of stress at the social level [53,54,55]. However, studies such as that of Queirós et al. have already used Xiaomi wearable devices for public health purposes [56].

In this study, levels of work stress will be evaluated, along with how it influences the occupational balance and routine of workers. For this purpose, one of the most widely accepted wearables among the population will be used—the Xiaomi Mi Band 3—whose minute-by-minute measurements will be obtained through a data acquisition system developed by the research group. Likewise, specific scales and questionnaires will be used to measure the different aspects that influence quality of life.

### Objectives

The main objective of this study is to assess the work stress level and its influence on the quality of life of workers at a research center.

The specific objectives are:—To itemise the level of some parameters, such as activity, sleep, and heart rate.—To determine the level and impact of occupational stress in worker’s daily life through the information from wristbands and questionnaires.—To identify patterns of occupational functioning, physical activity, and sleep in these people.—To study the association between the identified patterns of occupational functioning, activity, and sleep, and the level of occupational stress and quality of life.

## 2. Materials and Methods

### 2.1. Study Design

This project will be a pilot study to determine the viability, sample size, cost, and duration of the study. Additionally, this project has been designed in order to “demonstrate that the planned measurements, the data collection instruments, and the data management system are feasible and effective” [57]. If this study proves to be successful, it will be performed with a larger sample from different work settings.

This study will be observational, analytical, and longitudinal. That is, in this study, different variables of the population under study will be observed and recorded without intervention, and with the aim of establishing causal associations between variables. It is considered longitudinal because the variables will be followed for six months, with continuous recording and monitoring of physical activity and the quality of sleep (wristbands). Variables related to work stress, quality of life, and perception of the quality of sleep and the level of physical activity (specific evaluation tools) will also be specifically measured [57]. This study protocol will follow the SPIRIT 2013 guidelines (See File S1) [58].

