### 2.6. Data Collection and Management

Prior to any other data, socio-demographic features of the participants considered as relevant will be collected using a record sheet of our own elaboration. This questionnaire includes questions regarding age, gender, marital status, residential environment, cohabitation unit, educational level, profession, socio-economic level, working hours, overtime working hours, level of perceived stress, other non-work-related stress factors, actions oriented to stress reduction, and medication intake.

Data will be collected from different sources (Figure 1). For biometrical data, a Xiaomi Mi Band 3 will be worn by all the participants for six months to measure their physical activity (steps), sleep (hours of sleep and sleep stages), and heart rate (bpm). A self-developed data collection system will be installed in one of the computers of the research center, capturing the data from the wristbands via Bluetooth every time they walk nearby and storing it in an Structured Query Language (SQL) database [59]. When the data is analyzed, it will be retrieved by the SQL database in which it was stored. The data will be exported through CSV in a detailed or accumulated way for analysis in any statistical program.

The Research Electronic Data Capture Consortium (REDCap), a safe web application to create and manage online surveys and databases [60], will be used to digitally create the questionnaires and tests explained below, which will be sent to the participants to fill out.

In this study, participants will complete a set of assessment tools and a self-made questionnaire associated with work overload, sleep, and physical activity. These assessment tools will be filled in at the beginning and end of the study, while the self-made questionnaire will be answered throughout the study. This information is shown in Table 1.

The scales to be completed are: (1) the EQ 5D-5L, which evaluates mobility, personal care, daily activities, pain/discomfort, anxiety/depression, and global status at the moment of assessment [61], (2) the PSQI, which analyzes the quantity, quality, duration, latency, and efficiency of sleep [62], (3) the STAI, which evaluates the presence of anxiety [63], and (4) the PSS-10, which measures the degree to which, during the last month, people have felt annoyed or worried or, on the contrary, have felt confident in their ability to control their personal problems [64].

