### 2.7. Data Analysis

The statistical treatment of the data will be performed with the statistical package IBM SPSS Statistic version 22 (IBM, Chicago, IL, USA). The significance level for hypothesis testing is set at 5%. The numerical variables will be expressed as the mean (M) and standard deviation (SD), including range, minimums, and maximums, while the categorical variables will be shown with their absolute frequency and valid percentage. In addition to the simple description of the data and variables studied, inferential analyses will be conducted in order to determine possible significant relationships between the variables of the study, or to allow the contrast of hypotheses. The Kolmogorov–Smirnov test will be applied to check that the variables behave as a normal distribution [65]. If not, non-parametric tests will be used in the subsequent analysis. The association of numerical variables will be analyzed with the Pearson or Spearman’s Rho correlation test, depending on the distribution of the sample. To assess the association of categorical variables, the Chi-square test will be applied, or the likelihood ratio in the case that the frequencies observed are less than 5%. In the case of the association between quantitative and qualitative variables, the comparison of means will be made with Student’s *t*-test and analysis of variance (ANOVA) or Mann–Whitney and Kruskal–Wallis’ U test, as appropriate [66]. Finally, and in order to determine whether there are significant and relevant differences between the results of the evaluations performed (initial, intermediate, and final), the Wilcoxon test will be applied [66]. Data analysis includes the cleaning or pre-processing, description, and processing of the stored data. The final objective of these steps is to obtain information for decision making. During pre-processing, erroneous data are removed or corrected to avoid bias in the results. Subsequently, a descriptive statistical study which summarizes certain relationships and distributions in a simple way will allow us to choose which processing strategy to adopt.

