## 3. Discussion

This pilot study may allow us to design a broader study with more participants in future. Stress is increasingly present in our society, and despite being historically understood as an expected effect derived from the mere activity of working, in recent years it has started to be considered as detrimental, but not unavoidable [69,70]. This kind of study could help with the control and detection of stress, influencing positively its reduction and improving the quality of life of workers [37]. In particular, if this study is successful, it would allow the evaluation of occupational stress by using cheap devices and easy-to-understand questionnaires that can be used by any person without any specific training. It would be possible to establish the influence that working stress has on the daily routines and occupational balance of workers.

In addition to the worldwide increase in stress, the emergence of coronavirus disease 2019 (COVID-19) has meant a significant worsening of the mental health of a large part of the population. Stress, along with anxiety and depression, have spread or become more severe during the pandemic in the general population [71]. Job instability due to unforeseeable lockdowns and restrictive measures leads to increased stress in the population, which along with precarious jobs, generates long-term uncertainty that can further increase general stress levels [72,73].

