## 4. Conclusions

This project contributes to know the influence of occupational stress on the quality of life in a work environment. Therefore, it is intended to observe some parameters (activity, sleep, and heart rate) recorded through Xiaomi Mi Band 3. In addition, it aims to know about the level of work stress in diverse aspects of daily living, using various online self-report questionnaires in different periods of time. This data obtained from the questionnaires and wristbands will allow to determine the level of stress and its influences on quality of life during and after work.

The increasing use of portable devices such as smartphones or wearable devices encourages to obtain real-time biomedical data available for people, without going to health resources. Thus, this project considers as innovative that all measurements are registered online so that the workers can have an insight into their level of stress, the different stressful factors, and other parameters related to their activity, sleep, and heart rate, which influences their quality of life and work activity. It may help them to be more conscientious about their situation, so they can decide to make changes in their daily routines and habits.

Finally, considering the current pandemic situation, the online registration of all measurements will provide a follow-up of the participants without the need for face-to-face meetings.

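### Section 2.1 sets a causal aim, but the association tests named in Section 2.7 are all unadjusted and can support exploratory associations only

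*Protocol article*

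**What the plan says.** Section 2.1 states: "This study will be observational, analytical, and longitudinal". It then explains that variables will be recorded without intervention, "with the aim of establishing causal associations between variables".

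Related wording recurs. The main objective is "to assess the work stress level and its influence on the quality of life of workers at a research center". Section 2.5 defines the primary outcome as the influence of stress and anxiety on the worker. Section 3 says that if the study succeeds, "It would be possible to establish the influence that working stress has on the daily routines and occupational balance of workers". Section 4 again speaks of determining the influence of stress on quality of life.

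Section 2.2 gives one research centre and intentional sampling. Section 2.6 collects a record sheet before any other data. Besides age, gender and working hours, it covers "overtime working hours, level of perceived stress, other non-work-related stress factors, actions oriented to stress reduction, and medication intake".

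Section 2.7 sets a 5% significance level and assigns tests by type of variable. For two numerical variables: "The association of numerical variables will be analyzed with the Pearson or" Spearman coefficient. For two categorical variables, chi-square or the likelihood ratio. For one of each, t-test or ANOVA, or Mann–Whitney or Kruskal–Wallis. For change across assessments, Wilcoxon. No record-sheet item is given a role as a covariate.

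**The concern.** The stated aim and the stated analysis do not match. In an observational study, a correlation between work stress and quality of life can arise because a third factor drives both, or because the outcome drives the exposure. Poor sleep, for example, may raise stress as well as follow from it. The tests listed in Section 2.7 separate none of these explanations.

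Stress from outside work is the clearest example of a third factor. It may plausibly raise the answers to the work-stress items and also lower quality of life and disturb sleep. The protocol asks about it at baseline but does not say that it will be used.

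If the plan is followed as written, unadjusted pairwise associations could be reported as the influence of work stress. The larger study foreshadowed in Sections 2.1 and 3 would then be designed on that reading.

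**Working it through.** **Step 1: aim against analysis.** The article states no sample size, power or effect size, so there is no figure to reproduce. The check is to read each procedure in Section 2.7 for adjustment.

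| Procedure in Section 2.7 | Compares | Covariates described |
|---|---|---|
| Kolmogorov–Smirnov | distribution of one variable | not applicable |
| Pearson or Spearman | two numerical variables | none |
| Chi-square or likelihood ratio | two categorical variables | none |
| t-test/ANOVA or rank versions | one numerical, one categorical | none |
| Wilcoxon | one outcome between assessments | none |

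No association or comparison procedure is described with adjustment: no regression, partial correlation, ANCOVA, stratification or mixed model. The only open wording is that a descriptive look at the data will guide the later choice of processing strategy, which commits to no model.

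**Step 2: how large could the distortion be?** This is an illustration. Both inputs, a and n, are assumptions, as is the two-sided test, because the article does not state sidedness.

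Let one shared cause have correlation a with stress and a with the outcome, and let stress have no direct effect. Then

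- the marginal correlation is r = a × a;
- the partial correlation given the shared cause is (r − a²)/(1 − a²) = 0.

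By the Fisher z approximation, the unadjusted test at 5% rejects with probability

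P = 1 − Φ(1.96 − m) + Φ(−1.96 − m), with m = atanh(r) × √(n − 3).

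Example, a = 0.5 and n = 50: r = 0.25, atanh(0.25) = 0.255, √47 = 6.86, m = 1.75. So P = 1 − Φ(0.21) + Φ(−3.71), about 0.417.

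| a | r | n = 30, formula | n = 30, simulated | n = 50, formula | n = 50, simulated |
|---|---|---|---|---|---|
| 0.3 | 0.09 | 7.6% | not run | 9.5% | not run |
| 0.4 | 0.16 | 13.4% | 12.8% | 19.8% | 19.8% |
| 0.5 | 0.25 | 26.4% | 27.8% | 41.7% | 42.1% |
| 0.6 | 0.36 | 49.9% | 51.4% | 73.4% | 74.6% |

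The simulation used 4,000 replicates and agrees with the formula. Widening n to 20 and 100 gives 7% (a = 0.3, n = 20) to 96% (a = 0.6, n = 100). A test adjusted for the shared cause would reject at about the nominal 5%.

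**Step 3: which record-sheet items could be adjusted for?** The article itself gives reasons for caution. The Introduction lists work overload and work schedules among the factors that give rise to work stress, so working hours and overtime may be part of the exposure. It also describes antidepressants and anxiolytics as treatments made necessary by the effects of work stress, so medication may be a consequence. Adjusting for either could remove part of the effect under study. Non-work stress factors, age and gender more plausibly precede work stress.

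**The case against.** The strongest defence is that this is a feasibility pilot reported in a condensed article. Section 2.1 states an aim, not a result. The fourth specific objective and all of Section 2.7 speak of association, and the Discussion sentence is conditional on success. Covariate lists and models are commonly left to an analysis plan that is not shown.

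Much of this stands, and it lowers the severity. The absence of a covariate list would not be a finding by itself. What remains is on the page: a causal aim, repeated as influence in the main objective and the primary outcome, beside a test-by-test analysis section that does not serve it.

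Four stronger readings are tempting, and the article does not support them:

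- A reader might infer that every planned test is an unadjusted test of two variables. Wilcoxon is not; it follows one outcome over time.
- A reader might infer that general stress on the PSS-10 is to be passed off as work stress. Section 2.5 and Table 1 present the PSS-10 simply as stress. Work stress has its own questionnaire, and two of its daily items in Appendix A refer explicitly to work-related reasons.
- A reader might infer from the remark in Section 4 that workers gain insight into their data, "so they can decide to make changes in their daily routines and habits", that the study is in effect an intervention. No feedback procedure or timing is described, so this does not follow.
- A reader might take the rejection rates above as properties of this study. They rest wholly on assumed values, and at a = 0.3 the inflation is small.

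**Conclusion.** The mismatch is real and of moderate importance. An observational, intentionally sampled, single-centre pilot analysed with the tests named in Section 2.7 can support exploratory associations only.

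The size of the bias cannot be stated from the article. With one shared cause correlated equally (0.3 to 0.6) with both variables, no direct effect, 30 to 50 workers and a two-sided test, the chance of a spurious significant correlation is about 8% to 75%, against a nominal 5%. The range is wide because it depends on figures the article does not give.

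Adjustment would narrow the gap between aim and analysis but would not make the study causal, since unmeasured confounding and reverse direction would remain.

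**What to change.** 1. **Wording.** In Section 2.1, replace the reference to causal associations with exploratory associations. Temper the claim in Section 3 about establishing influence, and the matching wording in Section 4. This costs nothing.

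2. **One adjusted analysis.** For the main work-stress association, add a partial correlation or regression with a short fixed set from the record sheet: non-work stress factors, age and gender. Leave out working hours and medication unless a causal rationale is stated. With one term each, three covariates take the residual degrees of freedom from n − 2 to n − 5, for example from 28 to 25 at n = 30 (assumed). The list must stay this short in a small pilot.

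3. **Time order, for sleep only (optional).** Relate the daily work-related items to the following night's wristband sleep within worker, accounting for the previous night's sleep. This uses data already collected, but it removes only confounding that is constant over time. It does not address quality of life, because Table 1 does not schedule the EQ 5D-5L daily. The cost is slightly more analysis.
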